## Abstract

**Background:**

The Northwestern University Center for Education and Research on Therapeutics (CERT), funded by the Agency for Healthcare Research and Quality, is one of seven such centers in the USA. The thematic focus of the Northwestern CERT is ‘Tools for Optimizing Medication Safety.’ Ensuring drug safety is essential, as many adults struggle to take medications, with estimates indicating that only half of adults take drugs as prescribed. This report describes the methods and rationale for one innovative project within the CERT: the ‘Primary Care, Electronic Health Record-Based Strategy to Promote Safe and Appropriate Drug Use’.

**Methods/Design:**

The overall objective of this 5-year study is to evaluate a health literacy-informed, electronic health record-based strategy for promoting safe and effective prescription medication use in a primary care setting. A total of 600 English and Spanish-speaking patients with diabetes will be consecutively recruited to participate in the study. Patients will be randomized to receive either usual care or the intervention; those in the intervention arm will receive a set of print materials designed to support medication use and prompt provider counseling and medication reconciliation. Participants will be interviewed in person after their index clinic visit and again one month later. Process outcomes related to intervention delivery will be recorded. A medical chart review will be performed at 6 months. Patient outcome measures include medication understanding, adherence and clinical measures (hemoglobin A_1_c, blood pressure, and cholesterol; exploratory outcomes only).

**Discussion:**

Through this study, we will be able to examine the impact of a health literacy-informed, electronic health record-based strategy on medication understanding and adherence among diabetic primary care patients. The measurement of process outcomes will help inform how the strategy might ultimately be refined and disseminated to other sites. Strategies such as these are needed to address the multifaceted challenges related to medication self-management among patients with chronic conditions.

**Trial registration:**

Clinicaltrials.gov NCT01669473.

## Background

According to the Institute of Medicine, more than 1.5 million preventable drug events occur each year in the USA [1]. A third of these occur in outpatient settings, at a cost of approximately $4.2 billion annually [1]. Ensuring safe medication use is likely to become increasingly important as the number of adults taking prescription medications has risen dramatically [2]. Nearly half of Americans take at least one prescription medication, and one in ten takes five or more drugs, an increase of 70% since 1999 [2].

Despite frequent use, many adults struggle to take medications, with estimates indicating that only half of adults take drugs as prescribed [3]. Medication use may be particularly challenging for diabetic patients, who must often manage multiple comorbidities and complex multidrug regimens. Patients with low health literacy and limited English proficiency are likely to experience even greater confusion and negative medication-related outcomes, emphasizing the need for innovative and effective strategies to promote positive medication-related outcomes in this vulnerable population [4-6].

To address these challenges, we designed a health literacy-informed, electronic health record based strategy for promoting safe and effective prescription medication use among English and Spanish-speaking patients with diabetes mellitus. This project is one of four thematically related projects within the Northwestern University Center for Education and Research on Therapeutics (CERT). Funded by the Agency for Healthcare Research and Quality, the ‘Tools for Optimizing Medication Safety’ CERT is one of seven such centers created to promote optimal use of medications and to raise patient awareness of drug risks and benefits. In this paper, we provide an overview of our intervention, summarize evaluation activities, and discuss the sustainability and potential dissemination of our novel strategy.

## Methods/Design

This study seeks to reduce the patient confusion that often leads to unintentional medication non-adherence or medication errors. To promote sustainability and dissemination, we are utilizing an electronic health record platform to automate the delivery of patient-centered medication information materials. The specific aims of the study are as follows: (1) to refine and field test an electronic health record strategy for generating and distributing low-literacy prescription information for English- and Spanish-speaking primary care patients with diabetes; (2) to assess the process of the electronic health record intervention and its fidelity for providing understandable and actionable prescription information for patients at the point of prescribing; and (3) to evaluate the effectiveness of the electronic health record-based strategy to improve medication understanding, reconciliation, regimen consolidation, and adherence, compared with standard care. We have an additional exploratory aim to examine the effect of the intervention on surrogate clinical outcomes; hemoglobin A_1_c, low-density lipoprotein cholesterol and blood pressure.

This study is being conducted at the University of Illinois Hospital and Health Sciences System, an urban, academic medical center located in Chicago, which uses Cerner Powerchart®, a common electronic health record system. Patients are enrolled from three primary care sites: a resident-staffed general medicine clinic, a medicine/pediatrics clinic, and a faculty primary care clinic. These clinics serve a diverse, low-income patient population that is approximately 65% African American and 20% Hispanic. An estimated 36% of general medicine clinic patients have limited health literacy. Adjusted for patient volume, approximately 25% of these low literacy patients have been diagnosed with diabetes. The current standard of care in this clinic is for patients to receive a basic after-visit summary that describes the medical visit and includes a list of medications prescribed to the patient according to the electronic health record. This summary has not been designed according to health literacy best practices and patient education materials are not routinely given as part of standard care.

We will recruit 600 patients from participating clinics in no set proportion and randomize each to receive either standard care or the intervention. Participants will be eligible if they: (1) are over 18 years old; (2) have a documented diagnosis of diabetes; (3) are currently taking at least three daily, chronic, non-PRN (not pro re nata) medications; (4) speak English or Spanish; (5) have no intention to change clinics within the next year; (6) score 4 or higher on a six-item cognitive screener [7]; (7) are, by self-report, primarily responsible for taking their own medications; and (8) were prescribed a new medication, or have a dose, refill, or frequency change of a current medication for hypertension, hyperlipidemia, or diabetes mellitus during their index clinic visit.

Potentially eligible patients (criteria 1 to 4 above) are first identified via a review of their electronic health records. A list of those patients with a clinic appointment scheduled within the next three months is then compiled and sent to clinic physicians via secure email. Physicians have the opportunity to indicate which potentially eligible patients should not be contacted, owing to severe illness or cognitive concerns. With physician approval, patients will be approached by the research assistant to confirm eligibility following their doctor’s appointment. Research assistants will speak with potential participants after receiving an electronic message that they have been prescribed a new medication or received a changed dose or frequency of a medication of interest. Eligibility criteria will be confirmed before patients provide written consent and are enrolled into the study. The study has been approved by institutional review boards at the University of Illinois in Chicago (2012–0262) and Northwestern (STU00064056) and is also registered on clinicaltrials.gov (NCT01669473).

Patients in the intervention arm will receive three electronic health record-generated items at their clinic visit: (1) a pre-visit medication list, (2) medication information sheets, and (3) a post-visit medication list. These materials were designed by study team members and incorporate health literacy best practices, with Lexile analyses confirming a readability level of <8th grade [8,9]. The medication sheets and pre-visit medication list were previously tested in a National Institutes of Health study (R18HS17220). All materials were translated into Spanish using a committee-based approach and pilot tested among English- and Spanish-speaking patients (*N* = 9) to ensure comprehensibility [10]. The materials are as follows:The pre-visit medication list is generated on check-in and includes all medications prescribed to the patient according to their electronic health record. It lists the dosage, frequency and indication for all medications. The instructions on the form ask patients to report how much of each medication they take on a daily basis and if they have any concerns (need refill, cost, and so on) for any of the drugs. Patients are then asked to add any additional prescription or over-the-counter medications they are using and to remove medications that they are no longer taking. Forms are designed to be shared with providers during the clinic visit to promote medication reconciliation.If the patient is prescribed a new or dose-adjusted medication for diabetes, hyperlipidemia, or hypertension, a medication information sheet for that medicine will print automatically in the patients’ preferred language (English or Spanish). The medication information sheet is a one-page, plain-language information sheet that describes the medication’s indication for use, general directions, and side effects. It is designed to be patient-friendly and to provide essential need-to-know information for each drug.Following the visit, patients receive an updated post-visit medication list, which reflects any changes made to the pre-visit medication list as a result of their visit that day. The post-visit medication list includes all of the patient’s medications, listing dosage, indication, and the times each medication should be taken. It is intended to help patients organize their regimen according to the Universal Medication Schedule [11]. The Universal Medication Schedule ‘grounds’ medication use by providing more explicit times to describe when medicine should be taken (morning, noon, evening, bedtime) [5]. This concept was reviewed and recommended by the Institute of Medicine, the US Pharmacopeia, and the National Council for Prescription Drug Programs as a health literacy best practice. Patients in the intervention arm will receive this post-visit medication list, while those in usual care will receive a standard ‘after-visit summary’ recently implemented at the University of Illinois Hospital and Health Sciences System to comply with meaningful use requirements [12]. This standard after-visit summary is the only educational print material that patients in the usual care arm routinely receive after their clinic visit.

We will interview each patient in person at baseline, immediately following the index clinic visit, and one month after the index visit. At 6 months, a chart abstraction will be conducted to extract clinical surrogate outcome data (hemoglobin A_1_c, blood pressure, and low-density lipoprotein cholesterol).

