### Analyses

A sample size of 600 patients, 300 in each arm, was determined for this research study based on sample size calculations for the outcome measure of medication understanding. Assuming an overall baseline rate of understanding of 65%, a sample of 300 patients per arm would enable the detection of an 11% absolute increase in medication understanding with 80% power. These differences were considered appropriate, based on the results of prior studies conducted by this study team [17,28,29]. This sample size also supports our exploratory analyses for the effects of the intervention on surrogate clinical outcomes. For example, a sample size of 600 provides adequate power (86%) to detect a difference of 3 mm Hg in mean systolic blood pressure by study arm, assuming a standard deviation of 12.

We will perform intent-to-treat analyses to determine the study results. Before conducting formal analyses, we will perform descriptive statistics to ensure adequate balance of patient characteristics across the two treatment arms (usual care and intervention) at baseline; *t* tests and *χ*^2^ tests will be used to evaluate differences across the two arms for continuous and binary variables, respectively. Generalized linear models will be used for data analyses using PROC GENMOD in SAS (version 9.2), specifying the logit link function for binary outcomes (medication understanding, reconciliation, adherence, and regimen consolidation) and the identity link function for continuous outcomes (blood pressure, hemoglobin A_1_c). The treatment group will be the independent variable of primary interest and will be modeled with usual care specified as the reference group. Any potential confounding covariates noted in the descriptive analysis will also be included in the models.

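### The pre-visit list is issued at check-in, but eligibility, approach and consent follow the visit, so entry can depend on arm and the intent-to-treat label is not secured

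*Protocol article*

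**What the plan says.** All of this is in the protocol article.

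- **Allocation (Methods/Design).** The trial will recruit 600 patients and "randomize each to receive either standard care or the intervention". The time of randomisation is not given.
- **Start of intervention (Methods/Design).** Intervention patients receive three items at the clinic visit. The first comes before the physician is seen: "The pre-visit medication list is generated on check-in". It asks how much of each drug the patient actually takes and "if they have any concerns (need refill, cost, and so on) for any of the drugs". It also invites additions and deletions, and it is meant to be shared with the provider during the visit.
- **Criterion 8 (Methods/Design).** Patients qualify if they have a new prescription, or a dose, refill or "frequency change of a current medication for hypertension, hyperlipidemia, or diabetes mellitus during their index clinic visit".
- **Approach and consent (Methods/Design).** With physician approval, "patients will be approached by the research assistant to confirm eligibility following their" appointment, once an electronic message reports a new drug or a changed dose or frequency. Then: "Eligibility criteria will be confirmed before patients provide written consent and are enrolled into the study".
- **First interview (Methods/Design).** The baseline interview takes place straight after the index visit.
- **Analysis (Analyses).** "We will perform intent-to-treat analyses to determine the study results".

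**The concern.** Randomisation protects a comparison when the patients analysed are those who were allocated, or a subset chosen without regard to arm. Here the events that admit a patient to the trial happen after one arm has already received part of its intervention.

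There are two possible routes to arm-dependent entry. First, the list puts actual use, refill need and other concerns in front of the provider just before prescribing decisions, and a prescribing decision is what criterion 8 counts. Second, patients are approached and asked for consent when the arm may be apparent to them and to the research assistant.

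Either route could make the enrolled intervention patients differ from the enrolled usual-care patients for reasons other than chance. This would affect all four key outcomes (reconciliation, understanding, regimen consolidation, adherence) and the exploratory clinical measures.

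**Working it through.** **Step 1: order of events at the index visit, as written.**

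| Order | Event | Who |
|---|---|---|
| 1 | Check-in: pre-visit list generated | Intervention arm |
| 2 | Physician visit: criterion 8 event occurs or not | All |
| 3 | Electronic message, then approach by research assistant | Patients with an event |
| 4 | Eligibility confirmed, consent, enrolment | Those who agree |
| 5 | Baseline interview | Enrolled |

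**Step 2: where randomisation can sit.**

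- Before event 1: the list can be delivered as described, but criterion 8, approach and consent all follow allocation and exposure.
- After event 4: entry cannot depend on arm, but the list cannot then be given to the intervention arm at check-in for the index visit.

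No placement satisfies the whole description and also keeps entry independent of arm by design.

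**Step 3: the plan's own sample-size figure.** Inputs from Analyses: 300 per arm, 65% understanding, 11-point increase, 80% power. Alpha is not stated; two-sided 0.05 is assumed.

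- 65% as the usual-care rate (65% v 76%): 269 per arm needed; power at 300 is 84.2%.
- 65% as the overall rate (59.5% v 70.5%): 294 per arm needed; power at 300 is 80.8%.

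The stated figure is reproduced and is not in dispute.

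**Step 4: size of a possible bias (assumed values, not in the documents).** Let s be the share of enrolled intervention patients who entered only because of the list, and q their rate of understanding apart from any treatment effect. Everyone else has 65%.

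- Bias: b = s × (q − 0.65).
- With no true effect, the intervention rate is p₂ = 0.65 + b, and SE = √[0.65 × 0.35/300 + p₂(1 − p₂)/300].
- Type I error = 1 − Φ(1.96 − b/SE) + Φ(−1.96 − b/SE).
- Power with a true 11-point effect: 65% v (76% + b), 300 per arm.

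| s | q | Bias (points) | Type I error | Power, true +11 |
|---|---|---|---|---|
| 5% | 45% | -1.0 | 5.8% | 76.3% |
| 5% | 85% | +1.0 | 5.8% | 90.2% |
| 10% | 45% | -2.0 | 8.0% | 66.9% |
| 10% | 85% | +2.0 | 8.1% | 94.3% |
| 20% | 45% | -4.0 | 17.4% | 45.4% |
| 20% | 85% | +4.0 | 18.1% | 98.6% |
| 30% | 45% | -6.0 | 32.9% | 25.7% |
| 30% | 85% | +6.0 | 35.2% | 99.8% |

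Last row worked through: b = 0.30 × (0.85 − 0.65) = 0.06; p₂ = 0.71; SE = √[(0.2275 + 0.2059)/300] = 0.0380; b/SE = 1.58; type I error = 1 − Φ(0.38) + Φ(−3.54) ≈ 0.352.

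The figures for q = 45% and q = 85% differ slightly because the variance of p₂ differs.

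**The case against.** The strongest reply is that the time of randomisation is never stated and that a condensed article may leave allocation to the full protocol. That stands. A reader might infer that the arm is certainly fixed before the visit and that the groups compared are certainly not randomised. The document does not go that far. It supports only the alternative in Step 2, in which one reading allows arm-dependent entry and the other contradicts the delivery of the list. Fuller detail could settle which applies, but the stated order of check-in, visit and consent would remain.

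Four other points have force:

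- **Refill.** The most explicit link from list to eligibility is the question about refill need. The message that prompts an approach names new drugs and dose or frequency changes, not refills, so a refill-only patient might never be approached. This weakens that route. Changes prompted by reported use or concerns remain possible, but the list's stated purpose is reconciliation, so their frequency is unknown.
- **Direction.** A reader might expect the list to draw in patients with poorer understanding, and so bias against the intervention. Nothing in the document fixes the sign, which is why the range is symmetric. Nor does it establish that the arms will end up unequal in size.
- **Detectability.** It would be too strong to say that no later analysis could reveal the selection. The planned baseline comparison and the arm sizes could show some of it. Adjusting for imbalances so noted cannot remove selection on unmeasured factors, and interview-based covariates are collected after exposure.
- **Concealment.** The article does not say whether the research assistant knows the arm. That silence is not itself a fault; it means only that this route cannot be excluded.

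**Conclusion.** The point holds as a problem of sequence. The recruitment and intervention descriptions need reconciling whichever way allocation was done. If the arm is set before check-in, the only reading under which the list is delivered as described, then entry to the analysed set can depend on arm, and unqualified intent-to-treat is not the right name for a comparison of enrolled patients.

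The size is not known. The range of -6 to +6 points against an 11-point target, and type I error of up to about 35%, rest on assumed shares of 5-30% and differences of up to 20 points. If the list admits almost nobody who would not otherwise have entered, and consent does not differ by arm, the bias is negligible. The document gives no means of telling, and that is the reason to collect counts by arm.

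**What to change.** 1. State when allocation occurs, and reconcile the recruitment and intervention descriptions accordingly.
2. Keep the research assistant unaware of arm until eligibility and consent are settled, as far as the materials in patients' hands allow.
3. Extract from the electronic record, by arm, the numbers allocated, checked in, meeting criterion 8, approached and consenting. Candidates already come from a record-derived list, and the article reports enrolment as ongoing, so this should be recoverable.
4. Compare enrolled patients by arm on variables recorded before the visit, and adjust or weight for them. Say plainly that this cannot remove unmeasured selection.
5. Describe the analysis as a comparison of enrolled patients by assigned arm, not as intent-to-treat without qualification.
6. Reconcile refill in criterion 8 with the recruitment message and the information-sheet trigger, neither of which names it.

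The cost of items 2 to 5 is a change in approach procedure, a record extract, one extra adjusted analysis and a more modest label.

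Obtaining consent and randomising before check-in, then analysing everyone randomised, would remove the problem fully. It is a larger change while enrolment is under way. Dropping criterion 8 alone would not suffice: consent would still follow exposure, and patients recruited before and after the change would be selected differently.

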### Key covariates

We will collect data on a number of key covariates, including age, sex, English proficiency, comorbidities, medication and healthcare utilization, income, and race and ethnicity. Health literacy will be measured using the Newest Vital Sign [27].

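### Interview data labelled baseline are collected after intervention exposure has begun, and the imbalance-triggered adjustment rule does not exclude variables the intervention can change

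*Protocol article*

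**What the plan says.** The Methods/Design section sets the interview times: "We will interview each patient in person at baseline, immediately following the index clinic visit, and one month after the index visit". Read alone, the commas allow either two or three interviews. The abstract settles it at two: "Participants will be interviewed in person after their index clinic visit and again one month later".

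Recruitment fits this timing. With physician approval, "patients will be approached by the research assistant to confirm eligibility following their doctor’s appointment"; written consent comes after that.

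Delivery of the intervention starts earlier. "Patients in the intervention arm will receive three electronic health record-generated items at their clinic visit". The first item precedes the consultation: "The pre-visit medication list is generated on check-in". The form asks patients to add medicines missing from the list and to strike off those they have stopped, and it is meant to be shown to the provider. The last item comes at the end: "Following the visit, patients receive an updated post-visit medication list".

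The Analyses section describes arm comparisons by t and chi-square tests, intended "to ensure adequate balance of patient characteristics across the two treatment arms (usual care and intervention) at baseline". Possible confounders that come to light there are then added to the generalized linear models. The Key covariates section names age, sex, English proficiency, "comorbidities, medication and healthcare utilization, income, and race and ethnicity", and health literacy by the Newest Vital Sign. It introduces the list as examples, so the list is not closed.

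**The concern.** A baseline covariate is safe to adjust for because treatment cannot have affected it. Here the interview that carries the label comes after treatment has started, and the adjustment rule is triggered by a difference between arms. A variable that the intervention has moved is more likely to show such a difference than one it has not, so the rule tends to select the variables that should be left out.

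Adjusting for such a variable takes out of the treatment effect whatever part runs through it. It can also add bias if the variable shares unmeasured causes with the outcome. The rule applies to the models for understanding, reconciliation, adherence and consolidation, and to the exploratory clinical measures.

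**Working it through.** **The plan's own figure.** The timing issue does not change the stated sample size, which reproduces. Two-sided alpha of 0.05 and no dropout are assumed, since neither is stated. With n per arm = [1.960 × √(2p̄(1 − p̄)) + 0.842 × √(p₁(1 − p₁) + p₂(1 − p₂))]² / (p₂ − p₁)²:

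- 65% as the rate over both arms (59.5% v 70.5%): n = 294 per arm; power at 300 per arm is 80.8%, against 80% stated.
- 65% as the usual-care rate (65% v 76%): n = 269 per arm; power at 300 per arm is 84.2%.
- Systolic pressure, 3 mm Hg with SD 12: power 86.5%, against 86% stated.

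**Order of events in the intervention arm.**

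1. Check-in: pre-visit list produced. Exposure begins.
2. Consultation: list meant to be shared with the provider; information sheets printed for new or dose-adjusted medicines.
3. End of visit: post-visit list.
4. After the appointment: approach, eligibility check, consent, first interview.
5. One month: second interview.

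The article does not give the order of the post-visit list and the first interview. Step 1 alone is enough: no interview precedes exposure.

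**Which named covariates can the visit change?**

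| Covariate | Can the printed materials move it that day? |
|---|---|
| Age, sex, race/ethnicity, income, English proficiency | No |
| Existing comorbidities, past healthcare use | No, if they describe the period before the visit |
| Health literacy (Newest Vital Sign) | Unlikely; treated here as unaffected |
| Medication utilization | Yes: the form is built to add and remove medicines |

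**Form of the bias.** On a linear scale, adjusted effect = total effect − γ × δ. Here δ is the effect of treatment on the covariate as measured at the first interview, and γ is the covariate's association with the one-month outcome within arms. If δ = 0, as for the fixed traits, adjustment does no harm. For medication utilization the article gives neither δ nor γ. The sign is open too, because the form can lengthen or shorten the list. Suppose more medicines go with poorer understanding (γ < 0). A shortened list (δ < 0) then makes γδ positive and the adjusted effect smaller; a lengthened list (δ > 0) makes it larger.

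**The case against.** The strongest reply is that little in the covariate list is at risk. Most entries are traits that three printed items cannot change. The article does not say which covariates come from the interview and which from the chart, and patients are first identified through their records before the visit, so pre-visit values may be what is intended. For bias to arise, medication utilization would have to be measured after exposure, differ between arms because of treatment, be noted and judged a possible confounder, and be related to the outcome. All of that stands, and it limits the point to one named covariate and an open-ended rule.

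Three stronger readings are tempting, and the documents support none of them.

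- **Adjustment for first-interview understanding or adherence.** A reader might infer this from the word baseline. The article treats these measures only as outcomes and never lists them as covariates. If such an adjustment were made, the loss could be large. In a simulation that assumes a probit outcome, a true 65% v 76%, and a binary post-visit understanding measure with latent correlation 0.3 to 0.7, the adjusted difference is about 8 to 10 points if the measure already carries half the effect. If it carries all of it, the difference is about 6 to 9 points, and power at 300 per arm falls from 84% to about 32–68%. If treatment does not move the measure, the difference stays at about 11 points. These figures describe an analysis the article does not plan, so they do not size this point.
- **All materials received before the interview.** This is likely, but not stated for the post-visit list.
- **No pre-treatment comparison at all.** Fixed traits and prior diagnoses are pre-treatment whenever they are recorded. Whether post-visit eligibility and consent cause selection is a separate question.

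**Conclusion.** The concern holds in limited form. Interview data labelled baseline are post-exposure in the intervention arm, which follows from the article's own timings and needs no assumption. The adjustment rule, as written, does not keep treatment-affected variables out of the models. Medication utilization is the one named covariate that the intervention is designed to alter that day, so a difference caused by treatment could be flagged as imbalance and adjusted for. That step assumes that medication utilization is taken from the interview or from the chart after check-in, which the article leaves open.

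The size of any bias cannot be derived from the document, and its direction cannot be fixed in advance. It may be small. The case for acting rests on the rule being open-ended and the correction being nearly free, not on a demonstrated loss of effect. The stated sample size and power are unaffected.

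**What to change.** In Analyses, replace selection by observed imbalance with a pre-specified covariate set, limited to:

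- traits the visit cannot change: age, sex, language, race/ethnicity, income, health literacy;
- values from the electronic record as it stood before index check-in: medicine count, comorbidities, prior utilization.

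The arm comparison can stay as a description, but it should no longer decide what enters the models. In Methods/Design, call the first interview an immediate post-visit assessment, and state that no dosing, consolidation or adherence data collected there will be used as covariates.

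The cost is wording plus a small pre-visit record extract for patients already identified through the record. No visit or interview is added. The Trial status section says enrolment is still open, so the change can be made before the analysis. For patients already enrolled, it assumes that the record still shows values dated before check-in.
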